## Abstract

**Background:**

Data quality is vital for ensuring the accuracy, reliability, and validity of survey findings. Strategies for ensuring survey data quality have traditionally used quality assurance procedures. Data analytics is an increasingly vital part of survey quality assurance, particularly in light of the increasing use of tablets and other electronic tools, which enable rapid, if not real-time, data access. Routine data analytics are most often concerned with outlier analyses that monitor a series of data quality indicators, including response rates, missing data, and reliability of coefficients for test-retest interviews. Machine learning is emerging as a possible tool for enhancing real-time data monitoring by identifying trends in the data collection, which could compromise quality.

**Objective:**

This study aimed to describe methods for the quality assessment of a household survey using both traditional methods as well as machine learning analytics.

**Methods:**

In the Kilkari impact evaluation’s end-line survey amongst postpartum women (n=5095) in Madhya Pradesh, India, we plan to use both traditional and machine learning–based quality assurance procedures to improve the quality of survey data captured on maternal and child health knowledge, care-seeking, and practices. The quality assurance strategy aims to identify biases and other impediments to data quality and includes seven main components: (1) tool development, (2) enumerator recruitment and training, (3) field coordination, (4) field monitoring, (5) data analytics, (6) feedback loops for decision making, and (7) outcomes assessment. Analyses will include basic descriptive and outlier analyses using machine learning algorithms, which will involve creating features from time-stamps, “don’t know” rates, and skip rates. We will also obtain labeled data from self-filled surveys, and build models using k-folds cross-validation on a training data set using both supervised and unsupervised learning algorithms. Based on these models, results will be fed back to the field through various feedback loops.

**Results:**

Data collection began in late October 2019 and will span through March 2020. We expect to submit quality assurance results by August 2020.

**Conclusions:**

Machine learning is underutilized as a tool to improve survey data quality in low resource settings. Study findings are anticipated to improve the overall quality of Kilkari survey data and, in turn, enhance the robustness of the impact evaluation. More broadly, the proposed quality assurance approach has implications for data capture applications used for special surveys as well as in the routine collection of health information by health workers.

**International Registered Report Identifier (IRRID):**

DERR1-10.2196/17619

## Introduction

Data quality is vital for ensuring the accuracy, reliability, and validity of survey findings. Traditional approaches to monitoring data quality have sought to consider both the *intrinsic* (the data collection tool, implementation and support systems governing its use) and *extrinsic* factors (weather, enumerator-respondent dynamics, community environment) underpinning survey implementation, and in turn, data quality [1]. The quality of survey data starts with the selection of the survey institutions that will support the design and development, sampling, and implementation of the instrument. Decisions on survey tool content, including the selected indicators, language used, and phrasing of both questions and response options, as well as the length of the tool and the broader implementation strategy (tablets versus paper tools, sampling, training, profile, and the number of enumerators, workload), and support structures including supervision and reliability checks, may also influence quality.

Strategies for ensuring survey data quality have traditionally used quality assurance (QA) procedures—defined as “any method or procedure for collecting, processing or analyzing survey data that is aimed at maintaining or enhancing their reliability or validity” [2]. QA procedures usually focus on the intrinsic factors which influence data quality, starting with the sampling (overview of population composition, sampling frame, stratification, size), tool development (reliability of questions, accuracy, understandability of translation), enumerator selection (experience and profile) and training (length, methods, and content of training; enumerator and supervisor evaluation) [2]. These are followed by the piloting and refinement of tools and, ultimately, main survey implementation. QA procedures during implementation concentrate on survey personnel (enumerators, supervisors, coordinators), logistics (travel and team organization), contact procedures (respondent identification/ introduction, consent, refusal rates), enumerator remuneration, supervisor checking procedures, data transfers and checks [2]. Examples of QA procedures during implementation may include reliability checks from supervisors, site visits from senior study personnel, as well as routine data analytics.

Data analytics is an increasingly vital part of survey QA, particularly in light of the increasing use of tablets and other electronic tools which enable rapid, if not real-time, data access. Routine data analytics are most often concerned with outlier analyses that monitor a series of data quality indicators, including response rates, missing data, and reliability of coefficients for test-retest interviews. Dashboards may be used to visualize key tracking indicators and provide a snap-shot of survey implementation status. Collectively, while these procedures help ensure basic data quality, they fall short of optimizing the full potential of rapid data access borne from the use of electronic tools during survey implementation.

Machine learning is emerging as a tool with the potential to enhance real-time data monitoring by identifying trends in data collection that could compromise quality [3]. Machine learning covers a broad array of computationally-intensive methods aimed at detecting patterns in the data, including outliers and subtle trends that would not always be noticed via manual data cleaning and analysis. In the context of QA for survey monitoring, machine learning can be used to classify the data by the severity of outliers using either supervised techniques—with labeled training or pilot data—or a variety of unsupervised techniques [4].

Household surveys are expensive, time-consuming, and resource-intensive. Recognizing this, to date, applications of machine learning as part of household surveys have sought to reduce the expense of surveys by using satellite or phone data to predict socioeconomic distribution in a country [5]. However, little work has been done using machine learning techniques to improve the monitoring of surveys. To address this gap, we aim to outline a comprehensive strategy for monitoring the quality of data emerging from a large population-based household survey in rural India, including the use of machine learning techniques. Study findings are anticipated to shed light on the feasibility and effectiveness of advanced monitoring using machine learning as compared to traditional monitoring techniques.

## Methods

### Survey Description

In late 2018, as part of an impact evaluation of the maternal messaging program Kilkari, a randomly selected sample of 5095 women 4-7 months pregnant, with access to a mobile phone were identified across four districts of Madhya Pradesh, India: Rewa, Rajgarh, Hoshangabad, and Mandsaur [6]. Identified women were administered a structured baseline survey tool that sought to measure their knowledge of reproductive, maternal, newborn, and child health (RMNCH) practices and observe their digital literacy. Following the baseline survey, women were randomized to receive Kilkari messages or not (status quo). In this paper, we focus on the QA procedures for the endline survey administered to women enrolled in the study at 12 months postpartum. The endline survey will be used to capture RMNCH decision making, discussion, knowledge, and practice.

### Study Setting and Population

The study setting in Madhya Pradesh is characterized by disparities in access to education, mobile phones, and health services by gender and geographic location (rural/urban). With a population of over 75 million, Madhya Pradesh is home to over 20% of India’s population. Madhya Pradesh ranks as one of the worst-performing states in India economically (gross domestic product per capita of US $1100 versus US $1709 nationally) and in terms of health outcomes, particularly concerning child nutrition. In 2015, only 35% of children were breastfed within one hour of birth, and 58% of children were exclusively breastfed until 6 months [7]. While over half of pregnant women attended antenatal care (ANC) in the first trimester, only 36% received the recommended four ANC visits [7]. Health behaviors and care-seeking practices differ markedly between urban/rural areas and are underpinned by high rates of illiteracy (41% of women, 18% of men) and poor access to mobile phones among women [7]. In 2015, 19% of rural and 50% of urban women reported having access to a mobile phone [7].

Our trial population consists of women who have given birth in the past 1 year after being enrolled while they were  12-34 weeks of gestation, and all participants are at least 18 years of age, speak and understand Hindi, and own or have access to a mobile phone during the morning or afternoon. Our sample ranges from the ages of 18-44 years, with 61% of the sample being between the ages of 20-25. In terms of socioeconomic profile, 21% of our sample is “general class,” which is socially privileged, 47% are “other backward class,” which is somewhat marginalized, and the remainder are from highly marginalized groups—scheduled caste (20% of the sample) and scheduled tribe (11% of the sample). Hindu individuals comprised 95% of the trial sample, and 11% had not received any formal education, 6.5% had 1 to 4 years of schooling, 17.8% had between 5 and 7 years, 56.0% had between 8 and 12 years, and 8.7% had more than 12 years.

### Overview of Quality Assurance Procedures

The household survey monitoring strategy aims to identify biases and other impediments to data quality and includes seven main components: (1) tool development, (2) enumerator recruitment and training, (3) field coordination, (4) field monitoring, (5) data analytics, (6) data feedback loops for decision making, and (7) outcome assessment. In the framework below, we have outlined the processes we aim to complete in an effort to ensure survey data quality (Figure 1).

**Figure 1 figure1:**
[figure not shown]
Conceptual Framework of methods to improve data quality from Kilkari womens’ household survey.

#### Tool Development

Tool development assumed six essential steps: (1) linking intervention content with key indicators across behavior change outcomes for decision making, discussion, knowledge and practice, (2) drawing survey content from standardized and/or validated survey tools, literature, and/or expert review, (3) translation, (4) cognitive interviewing, (5) pilot testing, and (6) computer-assisted personal interviewing (CAPI) checking.

Our tool development began with looking at our key indicators on knowledge, practice, discussion, and decision making around topics relevant to pregnant and postpartum women such as family planning, infant and young child feeding, and newborn care. We then chose to assess these indicators using selected questions from previously completed standardized surveys. These questions were reorganized, reworded, and translated. The survey was a close-ended quantitative survey with single-answer multiple-choice questions as well as multiple-answer multiple-choice questions. Questions for which other options could be provided had an “other specify” text box. We chose to go beyond the traditional pilot testing methods and also use cognitive interviews to test our tools. Cognitive interviewing involves first asking the survey question as it is written, recording the respondent’s answer, then using verbal probes to determine if the respondent is understanding the question and providing an answer in the manner intended by the researchers [8]. We used this method to assess if our tool’s major sections on knowledge and behavior of family planning and infant and young child feeding were accessing the cognitive domains we intended them to [9]. Through this work, we revised our questions to improve their comprehensibility for our sample population (women in rural Madhya Pradesh).

During training, we spent time reviewing the paper versions of the tool as well as ensuring that our CAPI tablet versions, programmed using CSPro software, mirrored them well and adhered to the skip logic we had outlined. Both paper and tablet versions of the survey took on average about 1.5 hours to complete. The tablet version of the survey had just one question at a time appear on the screen. The process of checking the tablet version of the tool continued before and after piloting these versions in the field to ensure we had made all necessary changes in both language and logic before data collection with our end-line sample began. All survey data will be collected on tablets.

As part of the tablet-based data collection forms, we added a few parameters that were not part of the paper tools. These included time-stamps for the start and end of modules and time flags at the beginning and end of questions involving in-depth probing. GPS fields were added to the end of the tablet-based tool to track location.

#### Enumerator Recruitment and Training

Enumerator recruitment depends on survey size and timeline, as well as the characteristics of the enumerator. The experience and characteristics, including age, gender, caste, ethnicity, education, and geographic origins of an enumerator can influence not only their understanding of survey questions but also the implementation of the survey, including how they explain questions to and interact with respondents. Survey enumerators will be women fluent in Hindi, between 21-35 years of age, with education levels ranging from current college students to current PhD students, and 0-12 years of survey experience. To monitor the effects of enumerator characteristics and experience on data quality, we will start by administering a short survey during training to formulate their profile, and then as survey data are collected, use these profile data to understand potential associations between profile data and survey data quality.

To ensure that adequate numbers of enumerators are recruited, we have projected the number of interviews that need to be completed weekly by geographic area and considered the time it takes to administer each survey coupled with the time required to travel to and locate respondents. Additional factors such as enumerator attrition, along with the need to conduct repeat visits to locate respondents or complete partially completed surveys, will be factored in.

Once an adequate number of enumerators and supervisors are recruited, training will be key to optimizing survey implementation and ensuring data quality. Training will be led by the in-country field manager, a physician with >30 years of survey management experience. Additional support will be provided by study team members who participated in the development of the tool in its early stages. The training spanned 14 days and involved classroom-based lectures, quizzes, role-playing exercises, and field-based piloting. The tool covered multiple modules, including family planning methods, infant and young child feeding, and the immunization schedule. First, the didactic lectures covered the information on the domains covered in the tool. Then the field manager, along with support from various members of the study team who were instrumental in developing the tool, walked through the tool, including the questions, responses, and how to administer the question in a detailed manner. The session leader verified the data collectors’ understanding and asked them to clarify any lingering questions they may have had. After explaining and discussing the questions with the group, the enumerators conducted mock-interviews amongst themselves. A few quizzes on these topics were administered to ensure that the enumerators and supervisors were familiar with these health areas and associated vocabulary. In order to provide more real-world practice, there were two field pilot days in nearby villages that resembled the study population but were outside the study population, one with paper forms and another with the tablet version of the surveys with which the enumerators could practice. These pilot test days allowed the enumerators to become comfortable using the tool with live respondents, as well as allowing them an opportunity to comment on any issue in the tool, including language and flow.

#### Field Coordination

Beyond the development of the tool and enumerator selection and training, the quality of data is improved by strong field coordination. Field coordination is built on two main components: field and logistics planning as well as coordinating the monitoring of data collection through supervisors and checks. First, key eligibility criteria for interviews need to be kept in mind when planning field logistics. Women will be interviewed if they have completed 12 months postpartum or longer; thus, field planning will require that enumerators be spread across four districts of Madhya Pradesh to capture women as they reach their expected date of eligibility. Confirming women’s eligibility will require reliability monitoring, as outlined below. Once an eligible woman is identified, supervisors are given her identification and location information so they can coordinate their team of enumerators to her location and manage any follow-up visits as necessary depending on her availability.

A clear hierarchy in quality assurance activities as part of field operations is key for ensuring the collection of high-quality data. The field team will include 35 enumerators, 9 supervisors, and 2 coordinators, a survey coordinator, and a field manager. The male supervisors will be paired with a team of enumerators, consisting of 3-4 female enumerators, and will be in charge of checking the data as it is collected. The coordinators track adverse events and logistics and will conduct spot checks. The survey coordinator will monitor the data and relay any issues back to the larger research team. The field manager will handle training as well as ensure the field plan is in place. With clear roles in place, the field manager and survey coordinator will be best able to plan the fieldwork and monitoring, respectively. The data flow and feedback processes are outlined below (Figure 2).

**Figure 2 figure2:**
[figure not shown]
Data flow and feedback in Kilkari women’s survey.

#### Field Monitoring

Field monitoring consists of both confirming the eligibility of respondents as well as spot checks. Both these aspects happen at each of the five levels of field hierarchy: (1) enumerator, (2) immediate field supervisor, (3) coordinator, (4) field-level data quality supervisor, and (5) back-end data quality supervisor. At the enumerator level, any issues or red flags identified by enumerators will be reported back to their immediate supervisor who assigned them to the interview; these could include issues of eligibility or issues with tablets or other interview processes. Immediate field supervisors will focus principally on locating respondents and monitoring interviews. The former occurs based on the respondents the field coordinators give each supervisor—the respondent is located, and eligibility is confirmed. Then the supervisor may monitor part or all of the interview either through spot-check observation or form check and keep track of completion or any needed follow-up visits. The coordinators will manage larger village/block level logistics to ensure all eligible participants in an area have at least been visited once on a trip and also complete random spot-checks as their logistics duties allow. The field level quality supervisor will complete spot-checks as well as follows-up on any systemic issues found in both eligibility checking or back-end data monitoring either by individually speaking with enumerators/supervisors or discussing any data quality issues during debriefing meetings with the team. Finally, the back-end data quality supervisor will check weekly data uploads for any entry errors relating to eligibility, such as incompatible birth age or incorrect unique identifier. They will also assess mechanistic indicators such as time to interview completion or rate of skips or “don’t know” responses that warrant further observation of participating enumerators. The larger research team will conduct monthly checks on the field teams.

Beyond eligibility confirmations and observation spot-checks, our second stage of reliability monitoring will involve a 10% resample to ensure enumerators are asking the questions correctly so that we are getting consistent answers. A set of 15-25 questions will be randomly selected from a bank of 30, and the 10% sample will also be randomly selected from the total eligible population that has completed interviews. The recheck will be completed by a different enumerator either later in the day or a day later after the original interview has taken place.

#### Data Analytics

Data analytics will focus on descriptive and outlier analyses.

Descriptive analyses will focus on the conduct of basic frequencies across all questions in the survey to ensure that questions are not being unexpectedly skipped. Beyond checking the frequencies across the variables, we will also examine any anomalies, such as incorrect unique identifiers or ineligible respondents based on date, every week. These frequencies will be examined after each district in the survey is halfway complete.

The outlier analysis aims to identify anomalies in the data, which could indicate gaps in quality. Outlier analysis will start with the selection of features, and depending on these features and their distributions (parametric/non-parametric), several techniques will be explored for outlier detection including numerical outliers, Z-score, linear models, probabilistic and statistical models, as well as unsupervised machine learning (k-means clustering). Analyses will draw from the following data sources: enumerator completed survey tools from piloting, enumerator completed survey tools from the main field implementation, enumerator profile survey, and the recheck survey. The following steps will be undertaken:

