## Discussion

Machine learning has the potential to enhance routine QA methods for surveys, as well as the routine capture of health information through data capture applications. The proposed QA strategy for the Kilkari Impact Evaluation aims to comprehensively improve data collection quality through innovations in the tool development stage, such as cognitive interviewing, as well as in the monitoring stage through the use of machine learning. By complementing traditional monitoring back-end checks, machine learning has the potential to enhance survey monitoring by identifying biases in survey data collection, which may hamper data quality and, in turn, emerging findings. The potential use of automated feedback loops via text and email may serve to enhance the timeliness of feedback at the point of data collection and, in turn, improve efficiencies in data collection by minimizing the need to return to geographic areas after teams have left. The QA approach outlined in this protocol may have additional implications for study teams comprised of researchers spread across wide geographies, enhancing remote QA and enabling greater confidence in emerging data.

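### The all-question frequency check for unexpected skips is set at each district's halfway point, although data arrive weekly and other back-end checks are weekly

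*Protocol article*

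**What the plan says.** The Data Analytics section gives the purpose of the descriptive work as "basic frequencies across all questions in the survey to ensure that questions are not being unexpectedly skipped". The next sentence adds weekly checks of a different kind: "we will also examine any anomalies, such as incorrect unique identifiers or ineligible respondents based on date, every week". The timing of the frequencies follows: "These frequencies will be examined after each district in the survey is halfway complete".

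Field Monitoring describes the back-end work. It says that "the back-end data quality supervisor will check weekly data uploads for any entry errors relating to eligibility", and continues: "They will also assess mechanistic indicators such as time to interview completion or rate of skips". It gives no separate interval for the skip-rate review, whose stated use is to pick out enumerators who need further observation. On individual interviews it says that "the supervisor may monitor part or all of the interview either through spot-check observation or form check".

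Table 1 defines the skip indicator as a percentage over all skip opportunities in the whole tool, not question by question.

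**The concern.** A check for unexpectedly skipped questions is most useful early, when a fault in the tablet form or in how a question is asked can still be corrected cheaply. The plan places it at the middle of each district's fieldwork. The data needed for an earlier look are already uploaded weekly, and the article gives no reason for waiting.

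If one item is wrongly bypassed from the start, every interview up to the halfway table is exposed. The affected women must then be revisited, or the item must be analysed on fewer women. Revisits sit badly with the article's own interest in "minimizing the need to return to geographic areas after teams have left". A re-interview also gives an answer at a later date, which matters for time-bound items such as dietary recall.

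**Working it through.** The article gives no figure of its own on this point, so there is nothing to reproduce. The check has two parts.

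**1. What other controls would see.** Take a fault in a single item that affects all enumerators alike.

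- *Skip rate (Field Monitoring, Table 1).* The rate is pooled over the tool. If the tool has K skip opportunities per interview, a fault in one of them moves the pooled rate by at most 1/K. The article does not give K, but for a long multi-module tool the shift is small. Because the fault is common to all, it also makes no enumerator stand out.
- *Form checks, observation and spot checks (Field Coordination, Field Monitoring).* Supervisors check data as they are collected, so these could reveal the fault. However, interview monitoring is worded as optional, the coordinators' spot checks depend on their other duties, and none of these checks tabulates an item across interviews.
- *10% recheck (Field Monitoring).* It draws 15 to 25 questions from a bank of 30. Items outside the bank are not covered.
- *Pre-field checking (Tool Development; Enumerator Recruitment and Training).* Tablet skip logic was checked in training and around piloting, and one of the two field pilot days used tablets. This makes a fault less likely but does not detect one that gets through.

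The all-question frequency table is the one control that would show such a fault directly.

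**2. How many interviews come before the look.** Inputs are 5095 women (Abstract), four districts (Survey Description), and fieldwork from late October 2019 through March 2020 (Abstract, Results). Assumptions are equal districts, even accrual and full follow-up.

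Halfway table:
- Per district: 5095 / 4 = 1274; 1274 / 2 = about 637.
- All districts, if they run in parallel: 5095 / 2 = about 2548.
- If districts run in sequence, a tool-wide fault appears at the first district's halfway point: about 637 overall, and 637 / 5095 = 12.5%.
- If only 70% to 80% of women are reached (an assumption): 5095 × 0.70 / 8 = 446 to 5095 × 0.80 / 8 = 510 per district, or 1783 to 2038 overall.

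Weekly table, with the exact dates assumed:
- Longest period, 21 October to 31 March: 23.1 weeks; 5095 / 23.1 = about 220 per week, or 55 per district.
- Shortest period, 31 October to 1 March: 17.4 weeks; 5095 / 17.4 = about 292 per week, or 73 per district.
- The first look therefore comes at 4.3% to 5.7% of the sample.

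Ratio per district: 637 / 73 = 8.7 to 637 / 55 = 11.6, so roughly 9 to 12 times fewer interviews before the first look.

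If an item were permanently unusable for half the women, its standard error would rise by a factor of √2 = 1.41, or 41%. This too is a ceiling.

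**The case against.** A reader might infer that nobody looks for skips until a district is half done. The article does not support that. The back-end supervisor works on weekly uploads and also assesses skip rates. Supervisors check data during collection, spot checks occur at several levels, enumerators report tablet problems, and the wider team checks monthly. Module time-stamps could also reveal a skipped module. All of this stands. What remains open is the narrower case of a single item, common to all enumerators and outside the recheck bank.

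A reader might also infer that half of an item's data would be lost. That does not follow: Feedback Loops for Decision Making allows re-interview in serious circumstances, other checks may find the fault sooner, and a tool-wide fault would surface in whichever district first reaches halfway. Accrual need not be even either, since women enter as they reach 12 months postpartum. Nor do the documents support ranking this as the largest avoidable data loss in the plan.

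The wording is loose as well. The timing sentence follows one about weekly checks, and the article does not say that the halfway look is the only one. The natural reading is still that identifier and date anomalies are weekly and frequencies are at halfway. If weekly frequencies are intended, the text should say so. Finally, the remark about avoiding return visits is made about possible automated feedback by text and email, so it is context and not a commitment about the frequency tables.

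**Conclusion.** The point holds in a limited form. The only described control that examines every item across interviews for unexpected skips has a stated schedule much later than the weekly checks beside it. The other safeguards are pooled, directed at enumerators, discretionary, confined to a bank of 30 questions, or completed before fieldwork.

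Under the assumptions above, exposure before the check is up to about 637 interviews per district. Overall it lies between about 637 (sequential districts, tool-wide fault) and at most about 2548 (parallel districts). Field Coordination has enumerators spread across the four districts as women become eligible, which favours the parallel case but does not settle it. All these figures are upper bounds on exposure, not expected loss. Whether the later date was intended is not fully clear from the text; that it should be reconciled and moved earlier is.

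**What to change.** Reconcile Field Monitoring and Data Analytics so that each back-end check has one stated interval, including the skip-rate review. Run the item-level frequency and skip table on every weekly upload from the first week, by district and by enumerator, and compare each item's observed skips with those its skip logic should produce. Keep the halfway review as a fuller report.

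The cost is one more weekly table to set up, produce and read. Early tables by district and enumerator will have small cells, so they should prompt a look at the form or the item and not be read as estimates.
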